## **E8. Study Interventions**

### ***Question Prompt Sheet (QPS) (Appendix D)***

This is a single page, 25-item list of questions that was developed by an expert panel of clinicians in the Department of Palliative Care and Rehabilitation Medicine at the University of Texas M.D. Anderson Cancer Center using a 3 round Delphi process. Some of the questions were adapted from previous studies like the one by Clayton et al. The QPS consists of some of the most relevant questions in diverse aspects of palliative care and is intended for use by patients and caregivers attending an outpatient palliative care clinic.

### ***General Information Sheet (GIS) (Appendix E)***

This is a locally developed sheet created by the faculty in the Department of Palliative Care and Rehabilitation Medicine at the University of Texas M. D. Anderson Cancer Center for routine use at the supportive care center. It contains general patient information about palliative care and other related information felt to be of high relevance to patients. The length and content of the GI sheet are easy for the patients and families to read during the waiting period before being seen by the physician and/or nurse.

## **E9. Outcome measures**

### **1. Patients' perception of helpfulness in communicating with their physicians between a question prompt sheet (QPS) and a general information sheet (GIS).**

This will be assessed as the proportion of patients who agree or strongly agree that the information was helpful in the communication with their physician. It will be measured using the third item of the **Patients/ Caregivers Assessment Questionnaire** consisting of rating scales regarding the information material (**Appendix F**). Participants will rate the **perception of helpfulness** of the material using in a 5-point Likert scale from "strongly disagree" to "strongly agree" on item #3: "The material helped me to communicate with my doctor". It will also consist of 0 to 10 point scales assessing the extent to which the information material was helpful, was clear or easy to understand, had the right amount of information, was recommendable to other patients, did not make them anxious, enabled them to think of questions or concerns they hadn't thought of before, and a similar question sheet will be used by them before they see their doctor in the future. The questionnaire was developed from previous studies and through discussions between the authors. (J.A; E.B).

### **2. Caregivers' perception of helpfulness in communicating with their physicians**

**between a question prompt sheet (QPS) and a general information sheet (GIS).**

This will be assessed as the proportion of caregivers who agree or strongly agree that the information was helpful in the communication with their physician. It will be measured using item

#3 of the **Patients/ Caregivers Assessment Questionnaire (Appendix F)**

We will also assess other patients' and caregivers' views about the information material by using the **Patients/ Caregivers Assessment Questionnaire (Appendix F)** using the mean scores of the following patient and caregiver views:

- a. was helpful ( 0-10scale)
- b. was clear or easy to understand (0-10 scale)
- c. had the right amount of information (0-10 scale)
- d. was recommendable to other patients (0-10 scale)
- e. did not make them anxious (0-10scale)
- f. enabled them to think of questions or concerns they hadn't thought of before (0- 10 scale)
- g. a similar question sheet will be used by them before they see their doctor in the future (0-10 scale)

**3. Patients' and caregivers' overall satisfaction scores with the consultation with the use of between the QPS and the GIS.**

Patient satisfaction with the consultation will be assessed with the mean global satisfaction scores of the **Patient Satisfaction Questionnaire (PSQ)** which consists of 5-items with 0 to 100 Visual Analogue Scale (VAS), 0 being "not at all" and 100 being "extremely" (**Appendix G**). It measures patients' satisfaction with 1) how well their needs were addressed, 2) how actively involved they were in the interaction, 3) the adequacy of the information provided, 4) the adequacy of the emotional support provided, and 5) the overall consultation interaction. An overall satisfaction score is obtained by the average response on 5 items. The PSQ has been used to assess cancer patients' satisfaction with oncologist encounters in the inpatient and outpatient clinic settings. Internal reliability (Cronbach's  $\alpha$ ) of the PSQ in one study was 0.90^35.

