### **E4. Blinding**

Both the QPS and GIS will be concealed in opaque envelopes that will be identical to each other. The research staff and the patient/ caregiver will be blinded to the contents of the envelopes. The physician will also be blinded to the type of written material given to the patient. We successfully conducted this blinding protocol in a similar previous study.

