### **F. STATISTICAL CONSIDERATIONS**

The primary outcome is patients' perception of helpfulness (0-10 scale) in communicating with their physicians after the first consultation visit (Appendix F, Question 4). At patient enrollment, randomization will be obtained via Clinical Trial Conduct website. A total of 136 patients will be randomized into 2 groups (QPS and GIS) in the ratio of 1:1 to reach 128 evaluable patients with 5% attrition rate due to withdrawal or lost to follow-up. With 128 evaluable patients, we will have 80% power to detect a difference in means of 2 assuming the common standard deviation of 4 using two group t-test with a two-sided significance level of 0.05. We will also reach out to patients' caregivers to collect information if available.

Standard statistics including mean, standard deviation, median, range, frequency and percentage will be summarized for variables of interest, such as patients' demographics, clinical characteristics, anxiety state, patients'/caregivers' views about the information material, patients' satisfaction, physicians' views about the information material and consultation, patients' preferences for information, patient preferences for level of involvement in decision-making and patients' overall preference between the QPS and the GIS at the follow-up visit. Two sample t- test or Wilcoxon rank sum test, whichever appropriate, will be used to compare continuous variables of interest between the QPS and the GIS. Chi-squared test or Fisher's exact test, whichever appropriate, will be used to test for associations between categorical variables and helpfulness of information material (helpful vs the rest) for each of the QPS and the GIS as well as the preference in types of information material (QPS vs GIS).

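### The future-use item (item g) is worded around a question sheet that the GIS arm has not received when it answers, so its between-arm comparison is not like-for-like

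*Protocol*

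**What the plan says.** Section E9 describes one Patients/Caregivers Assessment Questionnaire (Appendix F) for both arms and mentions no GIS version. Besides the Likert item on communication, it has seven 0-10 ratings, summarised "using the mean scores of the following patient and caregiver views". Under outcomes 1 and 2 alike, the last of these is whether "a similar question sheet will be used by them before they see their doctor in the future".

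Section E8 describes the two materials differently. Of the QPS it says: "This is a single page, 25-item list of questions that was developed by an expert panel of clinicians". Of the GIS it says: "It contains general patient information about palliative care and other related information felt to be of high relevance to patients". Nothing in E8 describes the GIS as a list of questions.

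Under E6, Appendix F is completed after the first consultation. Patients are given both materials only in the open-label phase at the next follow-up visit.

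Section F names patients' and caregivers' views about the information material among its variables of interest. It then says that a two-sample t-test or Wilcoxon rank sum test "will be used to compare continuous variables of interest between the QPS and the GIS".

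**The concern.** Items a to f rate whatever material the respondent was handed, so they mean the same in both arms. Item g, as E9 words it, names a type of material, and that type matches only one arm. A GIS respondent has to decide what the phrase refers to: the sheet in hand, loosely described, or a list of questions that they did not have.

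At stake is the reading of one planned secondary result, intended future use, in patients and in caregivers. If the arms answer different questions, a difference between their means cannot be attributed to the materials. A larger sample does not help, and nothing described in the protocol records which reading a respondent took.

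**Working it through.** The question is one of wording, so the check is mainly a side-by-side reading.

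**1. What each arm holds when item g is answered (E6, E8)**

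| | QPS arm | GIS arm |
|---|---|---|
| Material received | 25-item list of questions | General information on palliative care |
| Does a question sheet describe it? | Yes | Not as E8 describes it |
| QPS seen before Appendix F? | Yes | No, only at the later open-label visit |
| Likely meaning of item g | Reuse of what was received | Reuse of what was received, or wish for a list not yet received |

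**2. Is the item compared between arms?** The link takes two steps. Section F puts these views among the variables of interest, then applies a between-arm test to continuous variables of interest. Item g is a 0-10 score reported as a mean, so the general sentence covers it. It is not named in the objectives or in the test-by-objective paragraph of section F.

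**3. Why the direction of bias is unknown.** Let μQ be the mean willingness of QPS respondents to reuse the QPS, and μG the mean willingness of GIS respondents to reuse the GIS. Let μH be the mean score given by GIS respondents who take the item to mean a question list, and p the fraction who read it so. For simplicity, take μG to be the same whichever way a GIS respondent reads the item. Then:

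- Like-for-like difference: μQ − μG
- Observed difference: μQ − [(1 − p)μG + pμH] = (μQ − μG) + p(μG − μH)
- Bias: p(μG − μH)

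If GIS respondents would welcome a list more than they would reuse the GIS (μH > μG), the bias is negative and the QPS advantage is understated, possibly reversed. If they score low because they had no such sheet (μH < μG), the bias is positive and the advantage is overstated. If p = 0 there is no bias. The documents give no value for p, μG or μH, so neither sign nor size can be computed.

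**4. How many answer the ambiguous form.** Section F plans 128 evaluable patients at 1:1, so 128/2 = 64 in the GIS arm. Their participating caregivers come on top; E1 allows up to 136 caregivers across both arms.

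**5. The plan's own sample-size figure.** For the primary outcome, section F uses a difference of 2, SD 4, 80% power and two-sided 0.05. The standardised difference is 2/4 = 0.5. The exact two-sample t-test then needs 63.8, so 64 per arm and 128 in total, with power 80.1%. Allowing for 5% attrition, 128/0.95 = 134.7, so 135 against the stated 136. The figure reproduces. It was set for the helpfulness score, not for item g, and nothing here alters it.

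**6. Position of the item.** The helpfulness items are item 3 (E9) and Question 4 (section F) of Appendix F. Item g is last in both E9 lists. E6 places Appendix F after the consultation, lists it after the repeat anxiety inventory and lists Appendix G (satisfaction) after it.

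**The case against.** The strongest objection is that Appendix F is not shown. E9 describes the ratings in the third person, so the printed items cannot read exactly that way. The two places where the phrase appears may be one paraphrase repeated. The only item E9 gives word for word, item 3, speaks neutrally of the material, so the printed future-use item may be neutral too. This stands and limits confidence. It does not clear E9, which defines the outcome and is not arm-neutral as written.

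A second objection is that the item is peripheral. It is one of seven other views, the between-arm test follows only from a general sentence, and outcome 7 asks directly which material patients prefer once they have had both. This also stands, and it is why the point is minor.

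A reader might infer more than the documents support:

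- *That the item unblinds GIS participants.* E4 says: "The research staff and the patient/ caregiver will be blinded to the contents of the envelopes". The item's phrase names no second arm and no other sheet, and a GIS participant can take it to mean the sheet in hand. At most it could hint that question sheets are of interest.
- *That it cues the primary items.* The consultation is over by then, and in the listed order both helpfulness items come before item g. Any hint would bear more plausibly on Appendix G, and even that is conjecture.
- *That the distortion can be expressed as a share of the 2-point planned difference.* No shift is documented, and that difference is the target for another item.
- *That GIS patients never receive a question sheet.* They do, at follow-up. The mismatch exists only when Appendix F is completed.

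**Conclusion.** The point holds in a limited form. As E9 words it, item g asks about reuse in the QPS arm and is ambiguous in the GIS arm, so the between-arm difference in its mean is not a like-for-like comparison, for patients or caregivers. The bias has unknown sign and no size that the documents can support.

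This rests on two assumptions: that the printed Appendix F carries E9's phrase or something close to it, and that the general comparison sentence in section F is meant to cover item g. If Appendix F is already neutral, what remains is a correction to the text of E9.

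Neither the primary endpoint nor the sample size is affected. Severity minor; confidence moderate.

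**What to change.** In E9, under outcomes 1 and 2, reword item g so that it fits either sheet, as items a to f do; for example, *I would use similar material before seeing my doctor in the future*. Confirm that Appendix F already reads this way, or amend it to match.

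If forms carrying the present phrase have been used, do not present item g as a between-arm comparison for those participants. The scores can still be described within each arm, with the wording stated.

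The cost is one phrase in the protocol and, if needed, one on the form, with no extra patients, visits or staff. The drawback is that answers given under the two wordings cannot be pooled for this item, so a late change leaves fewer participants for the comparison.

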**4. Physicians' views about the information material and the consultation:**

Physicians' views about the information material and overall satisfaction will be assessed by the mean scores of 3 questions (0-10 scale) soliciting the opinion of the physician regarding 1) the helpfulness of the information material to the patient, 2) its effect on the visit duration, and 3) the physician's overall satisfaction with the consultation, using a 0 to 10 Likert Scale (**Appendix H**).

**5. Effect of the QPS versus the GIS on the average speaking time of the patient or physician.**

This information will be extracted from the transcribed documents of the recording during the patient-physician clinical encounter. We will also measure the following outcomes from the same transcribed document:

- a) Total duration of the visit in minutes;
- b) Total number of questions asked by the patient and/or caregiver; and
- c) Categories of each question asked, namely: the palliative care team/services provided, symptoms and treatment, prognosis, end of life issues, or other.

**6. Association between the patient perception of helpfulness and demographic (age, gender, ethnicity, educational level, presence of a caregiver) and clinical characteristics (cancer stage, pre-consultation anxiety level, patient preferences for information, and patient preferences for involvement in decision-making).**

- a) Anxiety level will be measured by the ***Spielberger State Trait Anxiety Inventory*** (**Appendix A**) as described in Outcome #8 below.
- b) Patient preferences for information will be assessed using 2 items from the **Cassileth Information Styles Questionnaire** which assesses the amount of details and the type of information preferred by patients on a scale of 1 to 5. (**Appendix B**).

- c) Patient preferences for level of involvement in decision-making will be assessed using **The Control Preferences Scale**, a validated and reliable scale that measures patients' preferred level of involvement in decision-making during consultations with their physicians (**Appendix C**). The tool consists of statements describing different decision-making roles and patients are classified as preferring 'active', 'passive', or 'collaborative' roles in making decisions regarding their treatment based on their choices to those statements.

**7. Overall patients' preference between the QPS and the GIS.**

This will be measured by the proportion of patients who would prefer to use the QPS over the GIS in communicating with their physicians after having the opportunity to use both materials. We will use a multiple choice question: *"Now that you have had the opportunity to use the two different information materials, overall, which of them would you prefer to use in communicating with your doctor?"*. Patients will select their responses from 5 options (**Appendix I**).

**8. The change in patient's anxiety state from pre-consultation to post-consultation.**

Patients' anxiety state will be measured using the **Spielberger State Trait Anxiety Inventory (Appendix A)**. This inventory consists of two 20 item self-report versions which measure situational (state) and general (trait) anxiety. Each item consists of a 4-point Likert response scale. The state anxiety version will be used in this study to measure participants' situational anxiety before and after the consultation visit. Total score ranges from 20 to 80, where a score indicates greater anxiety. The inventory's simplicity makes it ideal for evaluating individuals with lower educational backgrounds. It's been found to have high reliability( $r = 0.93$ ), internal consistency, and validity.

**E 10. Distress Plan**

If any patient or caregiver experiences significantly high levels of distress while participating in the study, as per the clinical judgement of the palliative care physician, he/she will be taken off study and will be addressed by the physician, the palliative care counselor and/or other members of the interdisciplinary team as appropriate.

**E11. Patient Safety and Monitoring**

Patients will receive routine medical and nursing assessments from their assigned outpatient palliative care physician and clinical nurse during their visit in the clinic. In addition, our trained

research nurses will conduct study assessments and monitoring on the consultation day and the follow up day during the period when the study is being conducted. They will report any questions or concerns to the study physician who will be available by phone, email, or pager for further attention.

The principal investigator and the Institutional Review Board (IRB) will provide regulatory monitoring. Patient confidentiality will be ensured by use of unique study numbers, secure storage of clinical data, and anonymous reporting.

### **F. STATISTICAL CONSIDERATIONS**

The primary outcome is patients' perception of helpfulness (0-10 scale) in communicating with their physicians after the first consultation visit (Appendix F, Question 4). At patient enrollment, randomization will be obtained via Clinical Trial Conduct website. A total of 136 patients will be randomized into 2 groups (QPS and GIS) in the ratio of 1:1 to reach 128 evaluable patients with 5% attrition rate due to withdrawal or lost to follow-up. With 128 evaluable patients, we will have 80% power to detect a difference in means of 2 assuming the common standard deviation of 4 using two group t-test with a two-sided significance level of 0.05. We will also reach out to patients' caregivers to collect information if available.

Standard statistics including mean, standard deviation, median, range, frequency and percentage will be summarized for variables of interest, such as patients' demographics, clinical characteristics, anxiety state, patients'/caregivers' views about the information material, patients' satisfaction, physicians' views about the information material and consultation, patients' preferences for information, patient preferences for level of involvement in decision-making and patients' overall preference between the QPS and the GIS at the follow-up visit. Two sample t- test or Wilcoxon rank sum test, whichever appropriate, will be used to compare continuous variables of interest between the QPS and the GIS. Chi-squared test or Fisher's exact test, whichever appropriate, will be used to test for associations between categorical variables and helpfulness of information material (helpful vs the rest) for each of the QPS and the GIS as well as the preference in types of information material (QPS vs GIS).

For the primary objective and secondary objectives 2, 3, 4, 8, two sample t-test or Wilcoxon rank sum test, whichever appropriate, will be used to compare a) patients'/caregivers' perception of helpfulness in communicating with their physicians, b) patients'/caregivers' overall satisfaction with the consultation, c) physician's view/overall satisfaction about the information material and d) the change in patient anxiety state scores before and after consultation between the QPS and the GIS. For the secondary objective 5, two sample t-test or Wilcoxon rank sum test, whichever appropriate, will be used to compare the average speaking time of patient or physician during the consultation visit. Also, general linear model will be applied to assess the effect of QPS on the average speaking time adjusting for clinically and/or statistically important factors. For the secondary objective 6, univariate/multicovariate logistic regression will be used to evaluate patients' demographic and clinical factors on patients' perception of helpfulness of QPS when dichotomizing the answer to the question 3 in Appendix F ("Agree/Strongly Agree"=Helpful vs the rest). For the secondary objective 7, we will estimate the preference of information material with 95% confidence intervals. Also, univariate/multicovariate logistic regression will be used to evaluate patients' demographic and clinical factors on overall patients' preference between QPS and GIS.

Descriptive exploratory analysis of both the physician-patient visit transcripts and patient post-visit interviews will be led by an experienced qualitative researcher (LW) using MAXQDA11 (VERBI GmbH, Berlin, Germany) qualitative analysis software. As the first 10 physician-patient visits are completed for each treatment group (total 20 visits), initial coding of question categories and themes will be done (LW). The analysis team will then meet (LW, JA) and question types and themes will be reviewed for agreement and understanding. Each team member (LW, JA) will then code 5 visit transcripts from each treatment group (total 20 visit transcripts). The team will then meet again to review coding to be certain there is agreement. If there is disagreement in the coding an additional 5 interviews per treatment group per team member (LW, JA) will be coded and the team will then meet to confirm agreement. This process will continue until agreement is consistent. The remainder of the interviews will be analyzed equally by treatment group and team member.

Initial coding of themes will be conducted (LW) for the post-visit interviews.

The analysis team (LW, JA) will then meet and review the coding. Changes will be made to the coding until team consensus is reached. Modifications and additions to the interview guide may be made based on the results of each time point analysis. When all analyses of post-visit interviews have been completed, the team will meet to integrate themes from each time point and across the project. A final description of themes of patients' preferences for information to improve physician-patient communication will be developed.

Results of the analysis of the physician-patient visit transcripts and the patient post-visit interviews will be compared to determine common themes and develop a final description of patient perception of helpfulness of the material in enhancing physician-patient communication.

Other statistical methods, when appropriate, may be applied. Since this study is of minimal risk to the patient, we will not conduct an intermediate analysis.

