**A. OBJECTIVES**

**Primary**

1. To compare patients' perception of helpfulness in communicating with their physicians between a question prompt sheet (QPS) and a general information sheet (GIS).

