### **E3. Randomization**

Participating patients will be randomized in a double-blind fashion into one of two treatment groups: the active group will receive the QPS intervention and the control group will receive the GIS intervention. Randomization will be conducted via the Clinical Trial Conduct website developed by the Department of Biostatistics. We will randomize patients using Pocock-Simon's method and the randomization will be stratified by "physician" in order to carefully control for physicians' impact on patients' perception of helpfulness (primary endpoint).

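### Sections E9 and F define the measure for the primary objective differently (item-3 proportion versus Question 4 mean on 0-10), and the sample size and test fit only the second

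*Protocol*

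**What the plan says.** The primary objective in section A is "To compare patients' perception of helpfulness in communicating with their physicians between a question prompt sheet (QPS) and a general information sheet (GIS"). Section E3 calls this construct "patients' perception of helpfulness (primary endpoint"). Neither place fixes an item or a scale.

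Section E9, outcome 1, has a heading that repeats the objective and says that it will be "assessed as the proportion of patients who agree or strongly agree that the information was helpful in the communication with their physician". The rating is made on a 5-point Likert scale "on item #3: 'The material helped me to communicate with my doctor". The 0-10 rating of whether the material was helpful appears in E9 as further content of the same questionnaire. Under outcome 2 it appears again, in a list introduced by "We will also assess other patients' and caregivers' views about the information material" and summarised by mean scores.

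Section F declares: "The primary outcome is patients' perception of helpfulness (0-10 scale) in communicating with their physicians after the first consultation visit (Appendix F, Question 4"). The sample size there rests on a difference in means of 2 with a common SD of 4, a two-group t-test, two-sided 0.05, 128 evaluable patients and 136 randomised. The test is then assigned: "For the primary objective and secondary objectives 2, 3, 4, 8, two sample t-test or Wilcoxon rank sum test, whichever appropriate".

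For caregivers, E9 outcome 2 is "assessed as the proportion of caregivers who agree or strongly agree" on item 3. Secondary objective 2 falls under the same t-test or Wilcoxon sentence in section F.

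**The concern.** The two sections differ in the questionnaire item (3 or 4), the scale (5-point Likert or 0-10) and the summary measure (proportion or mean). A wrong item number alone cannot explain this, because a proportion agreeing on a Likert item is not a mean on a 0-10 scale.

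Two things are at stake. First, the two measures can give different answers. A report could cite the protocol for either one, so the choice could be made after the results are known. Second, the stated power supports only one of them. A reader who takes E9 as the definition of the primary endpoint has no sample size justification and no matching test.

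**Working it through.** **1. The plan's own figure.** Inputs from section F: difference 2, SD 4, two-sided 0.05, 64 evaluable per arm.
- Standardised difference: 2/4 = 0.5.
- Normal approximation: n per arm = 2 × (1.960 + 0.842)² / 0.5² = 62.8, so 63.
- Exact t-test: 63.8, so 64 per arm (128 in total), with power 80.1%.
- Attrition: 128/0.95 = 134.7, so 135. The stated 136 is the next even number.

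The calculation reproduces. It concerns the 0-10 mean only.

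**2. Where dichotomised helpfulness appears in section F.**
- Secondary objective 6: logistic regression for predictors, with item 3 dichotomised.
- Chi-squared or Fisher test: associations of categorical variables with helpful versus the rest, separately for each sheet. This is within arm, not QPS against GIS.
- Primary objective and secondary objective 2: t-test or Wilcoxon.

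No between-arm test of the item-3 proportion is stated. The item is not named in the t-test/Wilcoxon sentence, so a Wilcoxon test could be run on the raw 5-point answers. That would still not test the proportion that E9 defines.

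**3. What 64 per arm would give for the proportion.** The protocol states no arm rates, so these are assumptions. The 90% for QPS is borrowed, for illustration only, from the uncontrolled 30-patient study in the Background. With pooled rate p̄, power = Φ[(|p1 − p2| − 1.96·s0)/s1], where s0 = √(2p̄(1 − p̄)/64) and s1 = √((p1(1 − p1) + p2(1 − p2))/64).

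| QPS v GIS | s0 | s1 | (difference − 1.96·s0)/s1 | Power |
|---|---|---|---|---|
| 90% v 70% | 0.0707 | 0.0685 | (0.20 − 0.1386)/0.0685 = 0.90 | 82% |
| 90% v 75% | 0.0672 | 0.0658 | (0.15 − 0.1317)/0.0658 = 0.28 | 61% |
| 90% v 80% | 0.0631 | 0.0625 | (0.10 − 0.1237)/0.0625 = −0.38 | 35% |

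Across assumed GIS rates of 30, 40, 50, 60, 70 and 80%, the difference detectable with 80% power is about 24, 25, 24, 22, 20 and 16 percentage points.

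**4. Error rate if either version could be claimed.** With two tests at 0.05, the chance of at least one false positive cannot exceed 0.05 + 0.05 = 10%, and it falls as the items become more correlated. Simulation under no difference (64 per arm, a 0-10 score and a correlated binary item, assumed latent correlation 0.5 to 0.85, assumed helpful rate 50 to 90%) gives about 8 to 9.5%.

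**5. Caregivers.** The Question 4 declaration in section F covers patients only. E9 names item 3 for caregivers, and section F names no competing item or scale. The mismatch is between a proportion and a test for continuous or ordinal data.

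**The case against.** Only section F uses the words primary outcome with an item, a scale and a time point. It adds an effect size, a sample size and a test. E9 is a list of outcome measures and does not print the word primary beside outcome 1; its paragraph also mentions the 0-10 scales. On this view there is one declared primary endpoint, and E9 is loose drafting.

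Part of this stands: the protocol does not formally label two endpoints as primary, and section F is the more complete declaration. But the heading of outcome 1 repeats the primary objective, and no other E9 outcome addresses that objective. Its definition uses item 3 and a proportion, while the 0-10 helpfulness rating is listed among other views. A reader of E9 alone would analyse a different variable.

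Three stronger readings are tempting and not supported:
- **That the powered item measures the wrong construct.** E9 describes the 0-10 rating only as general helpfulness, but section F describes Question 4 as helpfulness in communicating. Appendix F is not shown, so this can only be a query.
- **That the protocol prescribes two primary tests and so inflates its error rate.** It assigns only the t-test or Wilcoxon test to the primary objective. The error rate in step 4 is conditional on someone exploiting the ambiguity.
- **That caregivers face the same two-item conflict.** Section F assigns them no rival item.

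**Conclusion.** The contradiction is in the current text and concerns the primary endpoint, so it must be resolved. It is not a detail that can wait for a statistical analysis plan, because the protocol itself fixes the measure in two incompatible ways.

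The sample size arithmetic is sound for the 0-10 mean. A reader might infer that the trial is underpowered, but the document does not support that. It supports only that no power is stated for the proportion. The 82%, 61% and 35% rest on assumed arm rates, and the family-wise error on an assumed correlation and helpful rate. These figures show the scale of the problem and are not properties of the plan. For caregivers the finding is limited to a proportion paired with an unsuitable test.

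**What to change.** Before outcome data are seen, name one primary endpoint (item, scale, summary measure and test) in the same terms in E9 and F.

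- **Option that keeps the stated sample size and test:** amend E9 outcome 1 to the 0-10 score on Appendix F Question 4. Make the item-3 proportion a named secondary endpoint, compared between arms by chi-squared or Fisher's exact test.
- **If the proportion is to be primary:** amend section F instead, with explicit rates for both arms, a test of proportions and a restated power. The required number of patients may then change.
- **Caregivers:** give the item-3 proportion a categorical test in section F.
- **Query:** confirm from Appendix F that Question 4 asks about help in communicating with the doctor.

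The first option and the caregiver change are wording amendments that need no extra patients or data. If the query shows that Question 4 asks something else, the remedy would go beyond wording and should be decided separately.
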